#### Strategies to improve adherence to interventions {11c}

This item is not applicable, since NIV is a resource which has its clinical indication established [15].

#### Relevant concomitant care permitted or prohibited during the trial {11d}

All concomitant care and interventions are permitted other than concomitant receipt of any other experimental treatment. Patients will use the drug therapy indicated by the attending physician. The NIV will be implemented by using a diving mask adapted into a mechanical ventilator, a HEPA filter in the expiratory branch, and a heat and moisture exchanger (HME) filter in the trachea Y, with it being performed twice a day for 60 min., with positive pressure levels of up to 10–12 cmH_2_O whenever there is a clinical indication to do so [12].

#### Provisions for post-trial care {30}

No special post-research regime is anticipated.

### Outcomes {12}

#### Primary outcome measure

OTI rate in patients with or without suspicion or confirmation of SARS-CoV-2 infection submitted to NIV with Owner mask or conventional orofacial mask.

#### Secondary outcome measure

In-hospital mortality [period: up to 30 days]Differences in the PaO_2_/FiO_2_ ratio regarding the baseline values (before NIV) [period: 48 h]Improvement in the PaO_2_/FiO_2_ ratio after beginning NIV [period: 1 h after NIV]PaCO_2_ levels [period: 1 to 12 h after NIV]Blood pressure (BP) and hypotension incidence (SBP < 80 mmHg or mean arterial pressure < 60 mmHg) [period: up to 2 h after NIV]Time between beginning NIV and its endICU time [time period: up to 30 days]Length of hospital stay of patients who used NIVAdverse events of the mask [period: obtained at pre-hospital discharge]Comfort of the patient with the mask (visual analog scale—VAS) [period: obtained at pre-hospital discharge]Satisfaction level (PGIC) after using NIV [period: obtained at pre-hospital discharge]NIV success rate with masks [deadline: 1 h since the beginning of NIV]Tidal volume (Vt), minute volume (MV), peak pressure (Ppeak), respiratory rate (RR), FiO_2_, inspiratory time (Ti), expiratory time (Te), air leak, inspiratory minute volume (VMi), and expiratory minute volume (VMe) obtained in NIV [period: 1 h after NIV]

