**Methods:**

A Brazilian multicentric study to assess patients admitted to the intensive care unit regarding their clinical, sociodemographic and anthropometric data. The primary outcome will be the rate of tracheal intubation, and secondary outcomes will include in-hospital mortality, the difference in PaO_2_/FiO_2_ ratio and PaCO_2_ levels, time in the intensive care unit and hospitalization time, adverse effects, degree of comfort and level of satisfaction of the mask use, success rate of NIV (not progressing to OTI), and behavior of the ventilatory variables obtained in NIV with an Owner mask and with a conventional face mask. Patients with COVID-19 and clinical signs indicative of RF will be submitted to NIV with an Owner mask [NIV Owner COVID Group (*n* = 63)] or with a conventional orofacial mask [NIV orofacial COVID Group (*n* = 63)], and those patients in RF due to causes not related to COVID-19 will be allocated into the NIV Owner Non-COVID Group (*n* = 97) or to the NIV Orofacial Non-COVID Group (*n* = 97) in a randomized way, which will total 383 patients, admitting 20% for loss to follow-up.

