### Objectives {7}

The primary objective of the study is to determine whether the use of Owner mask is effective in reducing the risk of OTI compared to conventional orofacial mask for patients with and without COVID-19 requiring NIV and the secondary objectives were to determine safety and effectiveness by comparing physiological measurements, mortality, length of stay measures, adverse effects, and patient satisfaction.

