#### Global Perception of Change

The Patients’ Global Impression of Change (PGIC) questionnaire will be used to assess the perception of improvement in individuals submitted to NIV use with the Owner mask before the patient’s discharge from hospital [27].

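### The satisfaction outcome is scored with the PGIC, which the protocol describes as perceived improvement, so it cannot isolate satisfaction with the mask

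*Protocol article*

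**What the plan says.** Four places in the protocol article bear on this outcome.

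- **Outcomes {12}, Secondary outcome measure** names the outcome and its instrument: "Satisfaction level (PGIC) after using NIV". The same entry sets the time of measurement as before hospital discharge.
- **Abstract, Methods** states what is to be captured: "degree of comfort and level of satisfaction of the mask use".
- **Objectives {7}** places it in the secondary objective, among "length of stay measures, adverse effects, and patient satisfaction", without mentioning the mask.
- **Global Perception of Change** is the only description of the instrument. It spells out PGIC as the Patients' Global Impression of Change and says that it "will be used to assess the perception of improvement in individuals submitted to NIV use with the Owner mask".

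Two other patient-reported measures are also taken before discharge and are listed as separate outcomes. One is a visual analog scale for comfort, and the other is an 11-question form on mask adverse effects.

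**The concern.** The outcome carries one name and the instrument is described as measuring something else. Satisfaction with an interface is a judgement about the interface. Perceived improvement is a judgement about the patient's own state. The two can diverge. A patient who disliked the mask but recovered may report marked improvement, and one who found the mask acceptable but was later intubated may report little.

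At stake is one secondary conclusion. If the arms differ in clinical course, the PGIC can differ for that reason alone, and the difference would be reported as greater satisfaction with one mask. Conversely, equal recovery in the two arms could leave a difference in satisfaction unseen on this score.

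**Working it through.** **Comparing the texts.** The finding rests on wording and depends on no figure in the plan.

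1. *Intended quantity.* The abstract ties satisfaction to use of the mask. The objectives speak of patient satisfaction in general, and the outcome list speaks of satisfaction after NIV. All three name satisfaction; only the abstract names the mask.
2. *Measured quantity.* The section describing the PGIC is headed "Global Perception of Change" and gives perceived improvement as what is assessed. It does not mention satisfaction.
3. *Any other source of a satisfaction score.* Comfort of the NIV face mask describes a comfort scale. Adverse effects of the NIV face mask describes a form on pain, leaks, dryness, pressure, irritation and claustrophobia. Both are informative about the mask, but neither is a satisfaction rating. The satisfaction outcome therefore rests on the PGIC alone.
4. *Timing.* The score is obtained before discharge, after NIV, any intubation and all concomitant care. A global rating given then can reflect all of these.

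**An illustration of how clinical course can enter the score.** The plan gives no figure to reproduce here. Inputs from Sample size {14} are control intubation rates of 30.2% (COVID-19) and 61% (non-COVID-19), and an absolute reduction of 20%, read as 20 percentage points. The Owner-arm rates are then 30.2 − 20 = 10.2% and 61 − 20 = 41%.

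Let g and i be the proportions rating themselves improved among never-intubated and intubated patients, the same in both arms. The values used for g and i are assumptions. Suppose also that satisfaction with the two masks is equal and that every randomised patient answers. Then

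proportion improved = p × i + (1 − p) × g,

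where p is the intubation rate, and the difference between arms is 0.20 × (g − i).

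| Stratum | g, i | Orofacial | Owner | Difference |
|---|---|---|---|---|
| COVID-19 | 0.8, 0.5 | 0.302 × 0.5 + 0.698 × 0.8 = 70.9% | 0.102 × 0.5 + 0.898 × 0.8 = 76.9% | 6 points |
| COVID-19 | 0.9, 0.3 | 0.302 × 0.3 + 0.698 × 0.9 = 71.9% | 0.102 × 0.3 + 0.898 × 0.9 = 83.9% | 12 points |
| Non-COVID-19 | 0.8, 0.5 | 0.61 × 0.5 + 0.39 × 0.8 = 61.7% | 0.41 × 0.5 + 0.59 × 0.8 = 67.7% | 6 points |
| Non-COVID-19 | 0.9, 0.3 | 0.61 × 0.3 + 0.39 × 0.9 = 53.4% | 0.41 × 0.3 + 0.59 × 0.9 = 65.4% | 12 points |

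Under these assumptions, a difference labelled satisfaction arises although the masks are equally liked. The illustration also reduces the PGIC to improved or not improved, which the protocol does not plan.

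**The case against.** Several points on the other side have weight.

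- **Perceived improvement may correlate with satisfaction.** It may, and a reader who inferred that the PGIC says nothing at all about satisfaction would go too far. The article does not state whether the question is anchored to the start of NIV or to admission, so the strength of any link is unknown. What stands is narrower: the protocol gives no basis for reading one as the other, and the score cannot separate satisfaction from recovery.
- **Only the abstract ties satisfaction to the mask.** This is correct. The objectives and the outcome list would also fit satisfaction with NIV in general. The mismatch remains on that reading, because perceived improvement is not satisfaction with NIV either.
- **Dislike of the mask would not go unrecorded.** A reader might infer that recovery could hide it altogether. The documents do not support that, since comfort and mask adverse effects are measured directly and separately.
- **The 6 to 12 points are not an estimate of bias.** A reader might take them as one. The improvement rates are assumed, and the score is taken before discharge, so patients who die in hospital cannot answer. The intubation gap among responders then need not be 20 points. And if one mask does reduce intubation, the resulting difference in perceived change is a real effect under the wrong name.
- **It is one secondary outcome among many.** It has no part in the primary outcome or the sample size. That limits its weight but does not remove the contradiction.

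Nor is this a detail that can be left to a separate analysis plan. The article itself fixes the pairing of outcome and instrument, and no later analysis can turn a collected improvement rating into a satisfaction rating.

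**Conclusion.** The point holds in a limited form. The outcome list calls the PGIC a satisfaction score, the abstract makes it satisfaction with the mask, and the description of the instrument makes it perceived improvement. Nothing else in the article measures satisfaction. As planned, the score cannot isolate satisfaction with the mask, and a difference between arms in clinical course can appear under that name.

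The direction of the effect follows if intubated patients report less improvement than others. Its size cannot be derived from the documents, and the finding does not depend on the illustrative figures. Only the satisfaction claim is affected; the comfort and adverse-effect outcomes are not.

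**What to change.** In the abstract, Objectives {7} and the list of secondary outcomes, rename the outcome patient global impression of change (perceived improvement), and draw no conclusion about satisfaction from it. Make the Global Perception of Change section agree. It now names only patients treated with the Owner mask and should cover both arms.

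To keep a satisfaction outcome, add one mask-satisfaction rating, for example from 0 to 10, before discharge in both arms. Ask it of every patient able to answer. It should not inherit the condition set for the comfort scale, which is limited to stable patients who responded well to NIV; that condition would leave out many of those in whom NIV failed.

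The cost is wording plus at most one extra question. Without the question, the trial gives up its satisfaction claim.

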#### Participant timeline {13}

The participant timeline is shown in Fig. 2.

**Fig. 2 Fig2:**
[figure not shown]
Study timelines of participants/interventions. * t_1_, start; t_2_, 1 h after; t_3_, 2 h after; t_4_, 24 h after; t_5_, 48 h after; t_x_, after the outcome; PaO_2_/FiO_2_, ratio of the partial pressure of oxygen in arterial blood (PaO_2_) to the inspired oxygen fraction (FiO_2_); OIT, orotraqueal intubation; ICU, intensive care unit; NIV, non-invasive ventilation

#### Sample size {14}

The calculated sample size is based on an OIT rate of 30.2% for patients with COVID-19 who require mechanical ventilation [17]. Thus, we estimate that a total of 126 patients (63 in each group) would provide 80% of power to detect an absolute reduction of 20% of the primary result [18], with the adoption of a two-tailed model and a significance level of 0.05. Assuming a loss of follow-up of 20%, 151 patients will be recruited.

Assuming an intubation rate of 61% for patients with acute respiratory syndrome requiring mechanical ventilation [19], we calculated that a total of 194 (97 in each group) patients would provide 80% power to detect an absolute reduction 20% of the primary result [18], with the adoption of a two-tailed model and a significance level of 0.05. Assuming a loss of follow-up of 20%, 232 patients will be recruited. The sample size calculations were performed using the G*Power software (Version 3.1.9.6) [20]. A total of 383 patients will participate in the study, 151 in the group of patients with suspicion or confirmation SARS-CoV-2, and 232 for those with respiratory syndrome who require non-invasive ventilation.

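### The 20% loss allowance was added as 20% on top of the evaluable numbers, so 151 and 232 recruits do not leave the 126 and 194 patients that the stated 80% power rests on

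*Protocol article*

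**What the plan says.** The section Sample size {14} of the protocol article sizes two strata separately, each at 80% power with a two-sided 5% significance level.

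- COVID stratum: "The calculated sample size is based on an OIT rate of 30.2% for patients with COVID-19 who require mechanical ventilation". The evaluable number follows: "we estimate that a total of 126 patients (63 in each group) would provide 80% of power to detect an absolute reduction of 20" percent. The recruitment target is then set: "Assuming a loss of follow-up of 20%, 151 patients will be recruited".
- Non-COVID stratum: "Assuming an intubation rate of 61% for patients with acute respiratory syndrome requiring mechanical ventilation". The evaluable number is 194, or 97 per arm, for the same absolute reduction. The recruitment target is: "Assuming a loss of follow-up of 20%, 232 patients will be recruited".

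The total is 383. The Methods paragraph of the Abstract gives group sizes of 63, 63, 97 and 97 and repeats the allowance: "which will total 383 patients, admitting 20% for loss to follow-up". Neither place gives another loss rate or another inflation rule.

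**The concern.** A loss to follow-up of 20% is a fraction of those recruited. To end with a required number N, one recruits N/(1 − 0.20). The protocol's targets look like N × 1.20, which offsets a loss of only 1 − 1/1.2 = 16.7%, and slightly less after rounding down.

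Three statements are therefore in conflict in each stratum: the recruitment target, the tolerated loss and the power. Any two can hold, but not all three. At stake is a power claim that fails at the attrition the protocol itself assumes, repeated in the Abstract where most readers will meet it.

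**Working it through.** **Inputs.** From Sample size {14}: control intubation rates of 30.2% and 61%, absolute reduction of 20 points (so 10.2% and 41% in the Owner arm), two-sided 0.05, 80% power, 20% loss, recruitment of 151 and 232. From Trial design {8}: 1:1 allocation.

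**Step 1: reproduce the evaluable numbers.** Two-proportion formula with pooled variance under the null and no continuity correction, where p̄ is the mean of the two rates:

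n per arm = [1.960 × √(2p̄(1 − p̄)) + 0.842 × √(p₁(1 − p₁) + p₂(1 − p₂))]² / (p₁ − p₂)²

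- COVID: p̄ = 0.202. n = (1.960 × 0.5678 + 0.842 × 0.5499)² / 0.04 = 62.07, so 63 per arm and 126 in total. Power at 63 per arm is 80.6%.
- Non-COVID: p̄ = 0.51. n = (1.960 × 0.7070 + 0.842 × 0.6927)² / 0.04 = 96.88, so 97 per arm and 194 in total. Power at 97 per arm is 80.0%.

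Both stated sizes reproduce. A continuity correction would give 72 and 107 per arm, and a one-sided test 49 and 77. A relative 20% reduction would need 851 and 260. The protocol's base calculation is therefore identified and sound.

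**Step 2: identify the inflation rule.**

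| Stratum | Evaluable N | N × 1.2 | Stated | N / 0.8 | Needed | Short by |
|---|---|---|---|---|---|---|
| COVID | 126 | 151.2 | 151 | 157.5 | 158 | 7 |
| Non-COVID | 194 | 232.8 | 232 | 242.5 | 243 | 11 |
| Sum | 320 | 384.0 | 383 | – | 401 | 18 |

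The stated figures are N × 1.2 rounded down. Rounding 232.8 down to 232 loses almost a whole patient even under that rule. The shortfall of 18 is 18/401 = 4.5%.

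**Step 3: what remains after 20% loss.**

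- COVID: 151 × 0.8 = 120.8, against 126.
- Non-COVID: 232 × 0.8 = 185.6, against 194.

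**Step 4: power at the planned recruitment**, with power = Φ{[√n × (p₁ − p₂) − 1.960 × √(2p̄(1 − p̄))] / √(p₁(1 − p₁) + p₂(1 − p₂))} and n the number left per arm:

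| Loss | COVID: n per arm, power | Non-COVID: n per arm, power |
|---|---|---|
| 10% | 67.95, 83.5% | 104.4, 82.9% |
| 15% | 64.2, 81.3% | 98.6, 80.7% |
| 20% | 60.4, 78.9% | 92.8, 78.3% |

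**Step 5: the loss that the targets do cover.**

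- To keep the stated evaluable numbers: 1 − 126/151 = 16.6% and 1 − 194/232 = 16.4%.
- To keep exactly 80% power, using the unrounded sizes: 1 − 124.14/151 = 17.8% and 1 − 193.77/232 = 16.5%.

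**The case against.** The strongest reply is that the error may never bite. Intubation is observed in hospital. Plans for assessment {18a} has data recorded for discontinued patients too, and the primary analysis is by intention to treat. Loss on this endpoint could be well under 20%, and at 10% or 15% both strata stay above 80% power. Even at 20%, the deficit is 1.1 and 1.7 points, probably less than the uncertainty in the borrowed control rates. This stands as a statement about size. It does not make the allowance right: the protocol chose 20% as its planning figure, and section {11b} takes some patients out of the study, so some loss is foreseen.

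A second reply is that 20% was meant as an add-on. The Abstract could be read so. The Sample size section cannot, because it names the percentage as the loss to follow-up. If an add-on was intended, the tolerated loss is misdescribed and still needs correcting.

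A third is that no power is stated for 320 patients as a whole. That is correct: 320 is only the sum of two strata powered separately, so the shortfall should be read by stratum, as it is above.

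A fourth concerns the approximation. Exact enumeration for the uncorrected chi-squared test moves unevenly with the sample size: 81.4% at 63 + 63 and 80.7% at 61 + 60; 80.7% at 97 + 97 and 79.6% at 93 + 92. This confirms that the loss of power is slight. It does not change the mismatch between the stated numbers, which is pure arithmetic.

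**Conclusion.** The error is confirmed and affects both strata. The recruitment targets were obtained by multiplying by 1.2, and at the stated 20% loss they leave about 121 of 126 and 186 of 194 patients. On the method that reproduces the protocol's own sizes, power is then 78.9% (COVID) and 78.3% (non-COVID) in place of 80%. The targets are 7 and 11 recruits below what a 20% loss requires.

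This is a correction to stated figures, not a serious loss of power, and it leaves the design and analysis untouched. It rests on the protocol's control rates and 20-point reduction, on loss spread equally over the arms, and on lost patients contributing no outcome. The non-COVID stratum has almost no slack (80.0% at 97 per arm), so a loss much beyond 16% takes it below target.

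**What to change.** Keep 383 and correct the wording of Sample size {14}. State that 151 and 232 recruits preserve 80% power in both strata for losses up to about 16%, and that power is about 79% (COVID) and 78% (non-COVID) if the loss reaches 20%. Change the Abstract so that it no longer presents 383 as covering a 20% loss. This costs wording only, adds no patients, and makes one stated figure slightly less favourable.

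If the sponsor prefers to keep both the 20% loss and 80% power, the targets become 158 and 243, 401 in total (402 with equal arms of 79 and 122). That is 18 or 19 more patients than planned, in a trial that Trial status shows had already begun recruiting.

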#### Recruitment {15}

Patients will be recruited from the designated hospitals for patients with and without COVID-19 with indication to receive NIV. The sample will be recruited non-probabilistically and by convenience, in which patients who meet the criteria for NIV institution will be selected according to the AMIB [12]. All hospitals involved in the study are a reference for the care of patients with or without COVID-19 and who need ventilatory assistance.

### Assignment of interventions: allocation

#### Sequence generation {16a}

The choice of the traditional orofacial mask or the Owner mask will be carried out by randomization performed using a random block table (10 patients per block) generated by the randomization.com program for patient allocation.

#### Concealment mechanism {16b}

Eligible patients will be allocated to receive NIV with Owner mask or conventional orofacial mask in individually numbered packs according to the sequential order provided by a person who will not be engaged in the study. Each treatment group will be coded and the allocation will be transferred to a series of opaque numbered envelopes for the patients selected for the study. The envelopes will be sent to the researcher responsible for the treatment phase.

#### Implementation {16c}

Patients will receive NIV through the Owner mask or the conventional orofacial mask according to the sequence of the previous randomization sent to each hospital. The choice of the traditional orofacial mask or the Owner mask will occur by randomization performed by a random table generated by a computer program that will determine the patient allocation group and the treatment allocation will be determined by the treating team opening the next sealed envelope. Both groups will be allocated to receive NIV by adapted mask or conventional mask with COVID-19 confirmed, or with other respiratory diseases. The random table will be the same for both groups of patients (with COVID-19 and/or another respiratory disease).

### Assignment of interventions: blinding

#### Who will be blinded {17a}

Only the data analyst will be blinded.

#### Procedure for unblinding if needed {17b}

Not applicable.

### Data collection and management

#### Plans for assessment and collection of outcomes {18a}

The data of each research subject (including discontinued subjects) will be registered in the database quickly, completely, and accurately through an electronic form made available to each researcher in their respective hospital and mandatory to be completed and checked by the researchers investigated by the study in each hospital institution. The data administrator will review and modify the data according to the check of the researchers where the research is being carried out.

Analysis of clinical, sociodemographic data, age, sex, and body mass index (BMI) will be performed. An analog pain assessment will subsequently be performed using the VAS [21] and the perception of effort using the Modified Borg Scale. Clinical severity will be quantified using the Simplified Acute Physiological Score III (SAPS III) based on data obtained from the patient’s medical record. The presence of comorbidities, smoking, symptoms, confirmation of SARS-CoV-2 infection, origin of the patient, history of exposure, and complications that may occur during hospitalization will be recorded. The OTI rate will be obtained in patients who have undergone NIV, as well as in-hospital mortality within a period of up to 30 days.

